# Salvage hypofractionated accelerated versus standard radiotherapy for the treatment of biochemical recurrence after radical prostatectomy (SHARE): the protocol of a prospective, randomized, open-label, superiority, multi-institutional trial

**DOI:** 10.1186/s13063-021-05708-5

**Published:** 2021-10-21

**Keywords:** Hypofractionated radiotherapy, Prostate cancer, Salvage radiotherapy

## Abstract

**Background:**

While several phase III trials have investigated the role of hypofractionated radiotherapy in the definitive treatment of localized prostate cancer, prospective data reporting the outcomes of hypofractionated radiotherapy in the postoperative treatment setting are sparse. Therefore, this study is designed to assess the efficacy and treatment-related toxicity of hypofractionated salvage radiotherapy for the treatment of biochemical recurrence in men who underwent radical prostatectomy. The primary objective of this trial is to investigate whether hypofractionated radiotherapy improves biochemical control compared with conventionally fractionated radiotherapy. In addition, treatment-related toxicity, quality of life, and survival will be evaluated as secondary endpoints.

**Methods:**

In this prospective, randomized, multi-institutional trial (the SHARE study), patients with intermediate- or high-risk prostate cancer will be randomized to receive either hypofractionated radiotherapy (65 Gy in 2.5-Gy fractions) or conventionally fractionated radiotherapy (66 Gy in 2-Gy fractions). Prostate bed irradiation or elective pelvic nodal irradiation including the prostate bed will be performed using intensity-modulated radiotherapy and daily image guidance. Treatment efficacy will be assessed using the serum tumor marker prostate-specific antigen, and toxicity will be evaluated through both physician- and patient-reported outcomes. Quality of life will also be investigated.

**Discussion:**

This study is designed to demonstrate whether hypofractionated radiotherapy is beneficial in terms of biochemical control and toxicity compared with standard salvage radiotherapy. If hypofractionated radiotherapy is shown to be superior to conventionally fractionated radiotherapy, it will mean that improved biochemical control can be achieved, accompanied by greater patient convenience and more efficient use of medical resources.

**Trial registration:**

ClinicalTrials.gov NCT03920033. Registered on 18 April 2019

## Background

After radical prostatectomy for the treatment of localized prostate cancer, approximately one-third of men will subsequently experience biochemical recurrence within a decade [1]. The risk of a rise in prostate-specific antigen (PSA) level was > 60% in patients with adverse high-risk features, such as Gleason score ≥ 8, serum PSA > 20 ng/mL, or stage of T3 or T4 [2]. Salvage radiotherapy (RT) is a potentially curative treatment option for biochemical recurrence following radical prostatectomy [3, 4].

Dose-escalated RT (76–80 Gy, 1.8–2.0 Gy per fraction) became the standard treatment for intact localized prostate cancer after several randomized trials demonstrated improved biochemical progression-free survival (bPFS) with this approach [5–7]. However, the potential benefit derived from dose-escalation in the postoperative setting remains to be clarified. The ASTRO/AUA guidelines recommend a minimum dose of 64–65 Gy with conventional fractionation in the postoperative setting, as the presumption is that the tumor burden is microscopic after prostatectomy, and therefore, a lower dose will be required in the postoperative setting versus the definitive setting [8]. However, several retrospective analyses have suggested that dose escalation during salvage RT may lead to improved biochemical control [9–13]. In a systematic review of 10,034 patients from 71 studies, the author noted that the dose response of salvage RT was similar to that of definitive RT of localized disease, and each increase of 1 Gy led to a 2% improvement in relapse-free survival [9]. Pisansky et al. evaluated 1108 patients who underwent salvage RT at 10 academic centers, demonstrating that doses > 66 Gy achieved superior biochemical control [13]. To date, the only phase III randomized clinical trial testing the dose escalation for salvage RT has been conducted by the Swiss Group for Clinical Cancer Research (SAKK). The SAKK 09/10 study compared dose-escalated RT (70 Gy in 35 fractions) versus standard-dose RT (64 Gy in 32 fractions) in the salvage setting. The initial results showed that dose escalation up to 70 Gy was associated with low rates of acute toxicity and had no impact on the recovery of early urinary continence or the prevalence of de novo incontinence [14, 15]. Freedom from biochemical failure, a primary endpoint of this trial, has not yet been reported.

For prostate cancer, pre-clinical and clinical data have shown that an *α*/*β* ratio of a tumor is low [16–18]. The *α*/*β* ratio of prostate cancer is 1.4–1.9 Gy, lower than the > 3 Gy reported for the surrounding normal tissues. This suggests that RT using hypofractionation (larger fraction size and fewer fractions) would increase the probability of tumor control without increasing treatment-related toxicities. In addition, recent advances in RT techniques, such as intensity-modulated RT (IMRT) and image-guided RT, have increased the potential for normal tissue sparing and improved toxicity [19, 20]. In the definitive setting, randomized trials of patients with prostate cancer receiving hypofractionated RT (HRT) versus conventionally fractionated RT (CRT) showed non-inferior or superior cancer control with HRT [21–25]. However, few randomized studies have evaluated the impact of HRT in patients with biochemical recurrence after prostatectomy. Several retrospective and phase I/II studies reported that HRT was tolerable in terms of toxicity and demonstrated encouraging results for cancer control in the postoperative setting [26–36]. The results of HRT using modern techniques, such as IMRT, volumetric-modulated arch therapy, or helical tomotherapy, in the postoperative setting are described in Tables 1 and 2. To date, despite clinical data suggesting a dose-response relationship in the salvage RT and radiobiological aspect of a low *α*/*β* ratio of prostate cancer, no randomized controlled trials have compared HRT versus CRT in the salvage setting.

**Table 1 Tab1:** Literature review of hypofractionated radiotherapy schemes for the treatment of prostate cancer in the postoperative setting

Study (ref.)	Design	Setting (patient number)	Total dose, Gy	Dose per fraction, Gy	EQD2 (prostate cancer^a^)	BED (early toxicity^a^)	BED (late toxicity^a^)
Tandberg [30]	Retrospective	Salv. (138)/Adj. (29)	65^b^	2.5	74.29	81.25	119.17
Kruser [33]	Retrospective	Salv. (108)	65	2.5	74.29	81.25	119.17
Lewis [31]	Retrospective	Salv. (43)/Adj. (13)	65^b^	2.5	71.43	78.13	114.58
Cuccia [32]	Retrospective	Salv. (38)/Adj. (37)	63.8	2.2	67.45	77.84	110.59
Barra [34]	Retrospective	Salv. (32)/Adj. (32)	62.5	2.5	71.43	78.13	114.58
Alongi [35]	Retrospective	Salv. (9)/Adj. (30)	70^b^	2.5	80	87.5	128.33
Saldi [27]	Phase I/II	Salv. (72)/Adj. (40)	72–74.25^c^	2.25	77.14–79.55	88.2–90.96	126–129.94
Katayama [26]	Phase I/II	Salv. (28)/Adj. (11)	54	3	69.43	70.2	108
Gladwish [29]	Phase I/II	Salv. (26)/Adj. (4)	51	3	65.57	66.3	102
Macchia [28]	Phase I/II	Salv. (18)/Adj. (106)	62.5	2.5	71.43	78.13	114.58
This study	Phase III	Salv. (288)	65	2.5	74.29	81.25	119.17

*EQD2* equivalent dose in 2-Gy fractions, *BED* biologically equivalent dose, *Salv.* salvage, *Adj.* adjuvant

^a^*α*/*β* ratio for prostate cancer is 1.5, 10 for early-responding normal tissue, and 3 for late-responding normal tissue

^b^Median

^c^Salvage

**Table 2 Tab2:** Literature review of hypofractionated radiotherapy outcomes for the treatment of prostate cancer in the postoperative setting

Study (ref.)	Median follow-up, months	bPFS, %	Toxicity scoring system	Acute toxicity, %		Late toxicity, %	
				GU	GI	GU	GI
Tandberg [30]	38.6	78.4^a^ (4 years)	CTCAE v4.0^b^/RTOG^c^	≥ G2: 22; G3: 1^d^	G2: 5; ≥ G3: 0	G2: 39; ≥ G3: 11	G2:10; G3: 1^d^
Kruser [33]	32.4	67 (4 years)	RTOG	G2: 6.4; G3: 1^d^	G2: 14; ≥ G3: 0	G2: 15; ≥ G3: 0	G2: 4; ≥ G3: 0
Lewis [31]	48	75 (4 years)	CTCAE v4.0^b^/RTOG^c^	G2: 4; ≥ G3: 0	G2: 4; ≥ G3: 0	G2: 39; G3: 28	≥ G3: 2^d^
Cuccia [32]	30	73 (3 years)	CTCAE v4.0	G2: 4; ≥ G3: 0	G2: 18; ≥ G3: 0	G2: 2.6; G3: 2.6	G2: 6.6; ≥ G3: 0
Barra [34]	15.5	Not reported	CTCAE v4.0^b^/RTOG^c^	≥ G2: 0	≥ G2: 0	G2: 3.3; G3: 3.3	≥ G2: 0
Alongi [35]	22.8	Not reported	RTOG	G2: 10; ≥ G3: 0	G2: 20; ≥ G3: 0	G2: 8; G3: 3	≥ G2: 0
Saldi [27]	27	Not reported	CTCAE v4.0	G2: 8.9; ≥ G3: 0	G2: 9.8; ≥ G3: 0	Not reported	Not reported
Katayama [26]	Not reported	Not reported	CTCAE v4.0	≥ G2: 0	G2: 17.9; ≥ G3: 0	Not reported	Not reported
Gladwish [29]	24	Not reported	CTCAE v3.0^b^/RTOG^c^	G2: 3; G3: 3	≥ G2: 0	≥ G2: 1^d^	≥ G2: 2^d^
Macchia [28]	30	86.5 (5 years)	RTOG	G2: 17.7; G4: 1^d^	G2: 24.2; ≥ G3: 0	≥ G2: 7.3	≥ G2: 1.1

*bPFS* biochemical progression-free survival, *GU* Genitourinary, *GI* gastrointestinal

^a^Patients with a 12-month minimum follow-up were analyzed for bPFS

^b^Acute

^c^Late

^d^Number of patients

The protocol of the Salvage hypofractionated accelerated versus standard radiotherapy for biochemical recurrence after radical prostatectomy (SHARE) study is outlined here. This prospective, randomized, multi-institutional trial is designed to assess whether HRT improves biochemical control versus CRT without increasing treatment toxicity in prostate cancer patients with biochemical recurrence after radical prostatectomy. This study uses two RT dose schemes, HRT (65 Gy in 2.5-Gy fractions) versus CRT (66 Gy in 2-Gy fractions).

## Methods/design

### Recruitment and study design

The SHARE study is a prospective, randomized, multi-institutional trial. The protocol was approved by the institutional review boards of two participating tertiary hospitals, the Asan Medical Center and Samsung Medical Center, where it is currently ongoing. A computer-generated randomization schedule assigns the patients to either the HRT (65 Gy in 2.5-Gy fractions) or CRT (66 Gy in 2-Gy fractions) arm (Fig. 1). Random assignment is performed with a 1:1 allocation using blocked randomization, with a random block size of 4. Patients will be stratified by intermediate or high-risk according to the National Comprehensive Cancer Network (NCCN) risk classification [37] using a computer-generated random allocation sequence to ensure concealment. The clinical research nurse keeps the original random allocation sequences using the Excel file locked with a password. The process of allocation concealment from primary researchers and participants is maintained until the time of assignment. Neither the investigators nor the participants are masked to the allocated arm because blinding is not possible. For adequate participant recruitment, the investigators fully explain to potential participants the purpose, design, potential risks, and benefits of this study, as well as general ethical issues. A monthly newsletter regarding participant enrollment will be made and sent to the principal investigator and clinical research coordinators of each institution. All patients must provide written informed consent.

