### Sample size considerations and statistical analysis

The trial is powered to assess the superiority of HRT when compared with CRT. Power calculations are based on an absolute increase in bPFS of 15% (from 50 to 65%) at 5 years following HRT compared with CRT according to the dose-response relationship described by King [9]. By postulating a minimum 5-year follow-up period and allowing 5% for loss, at least 144 patients per treatment arm (288 patients in total) are required, which achieves 80% power, with a two-sided *α* of 0.05. Subgroup analyses will be performed based on the risk group (intermediate vs. high-risk group), RT field size (prostate bed only vs. elective pelvic nodal irradiation), and use of ADT.

Statistical analysis will be conducted according to the intention-to-treat approach. Survival data, PSA value, toxicity, and QoL information will be collected even though participants discontinue the planned treatment. Multiple imputation method will be used for handling missing data. The chi-square test and Student’s *t* test will be used for categorical and continuous variables of patient characteristics, respectively. Time to biochemical progression will be calculated from the end of RT. The Kaplan–Meier method will be applied to estimate bPFS curves, and the log-rank test will be used to compare the curves between the two study arms. The Kaplan-Meier method and log-rank test will be used to investigate DMFS and CSS. Acute toxicity outcomes and QoL will be estimated using the chi-square test, and late toxicity outcomes will be determined using the Kaplan-Meier method.

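### The stated block scheme contradicts itself; read as blocks of 4 in an unmasked trial, it lets part of the allocation sequence be inferred, so concealment until assignment does not fully hold

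*Protocol article*

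**What the plan says.** All the relevant statements stand under Recruitment and study design in the protocol article.

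- Scheme: patients are allocated 1:1 "using blocked randomization, with a random block size of 4". No other block size is given.
- Stratification: "Patients will be stratified by intermediate or high-risk according to the National Comprehensive Cancer Network (NCCN) risk classification". Hospital is not named as a factor, although the trial runs at "two participating tertiary hospitals".
- Masking: "Neither the investigators nor the participants are masked to the allocated arm because blinding is not possible".
- Custody of the list: "The clinical research nurse keeps the original random allocation sequences using the Excel file locked with a password".
- Concealment: "The process of allocation concealment from primary researchers and participants is maintained until the time of assignment".

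The sample size section adds that "at least 144 patients per treatment arm (288 patients in total) are required". The article is dated 21 October 2021. Its Trial status section gives recruitment as August 2019 to an expected end in March 2022.

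**The concern.** A block size is random only if at least two sizes are possible, so the sentence cannot be right as it stands. If the only size is 4, anyone who has seen the earlier open-label assignments in a stratum knows the last assignment of every block, and sometimes the one before it. A claim of concealment up to the moment of assignment cannot cover those positions.

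What is at stake is who gets enrolled, and when. Patients within a risk stratum still differ in prognosis: entry PSA runs from above 0.2 to 1.0 ng/ml (Inclusion criteria), and hormone treatment and nodal irradiation are left to clinicians (Treatment implementation). The Discussion also records expectations that could steer a choice. Its authors expect good biochemical control with hypofractionation, and they cite acute grade 2 or higher genitourinary toxicity of 22% against 8% in a retrospective comparison. A clinician who could foresee the arm could bring a patient forward or hold one back. Intention-to-treat analysis does not repair this, because the selection happens before randomisation. An objective PSA endpoint does not repair it either.

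**Working it through.** The article gives no predictability figure to reproduce, so the size is derived from the scheme.

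**Inputs from the article:** 1:1 allocation, block size 4, no masking, two risk strata, two hospitals, 288 patients (288/4 = 72 blocks). **Not stated, so assumed:** what share of assignments an observer sees, and whether the hospitals share one list.

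**1. Observer who sees every earlier assignment in the stratum.** A 1:1 block of 4 has six equally likely orders. The best strategy is to guess the arm with more places left.

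- 1st position: guess right with probability 1/2.
- 2nd: two of the three remaining places belong to the other arm, so 2/3.
- 3rd: with probability 1/3 the first two were the same arm and the third is certain; otherwise it is even. So 1/3 × 1 + 2/3 × 1/2 = 2/3.
- 4th: always certain.

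Share certain = (0 + 0 + 1/3 + 1)/4 = 33.3%, or 72 × 4/3 = 96 of 288. Correct-guess rate = (1/2 + 2/3 + 2/3 + 1)/4 = 70.8%, against 50% with no information.

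**2. Observer at one hospital, one list shared by both.** Let a share p of assignments fall at the observer's hospital, and let K, binomial with 4 trials and probability p, be the number in a block. The observer's own 1st to 4th assignments in a block carry the same probabilities as in step 1. Block boundaries are assumed known, which favours the observer.

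Share certain = [P(K≥3)/3 + P(K=4)]/(4p)

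- p = 0.5: (0.3125/3 + 0.0625)/2 = 8.3%
- p = 0.7: (0.6517/3 + 0.2401)/2.8 = 16.3%

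Correct-guess rate = [P(K≥1)/2 + 2P(K≥2)/3 + 2P(K≥3)/3 + P(K=4)]/(4p)

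- p = 0.5: (0.9375/2 + 2×0.6875/3 + 2×0.3125/3 + 0.0625)/2 = 59.9%
- p = 0.7: (0.9919/2 + 2×0.9163/3 + 2×0.6517/3 + 0.2401)/2.8 = 63.6%

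Simulation of the same set-up agrees (8.3% and 16.4% certain; 59.9% and 63.6% guessed).

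**3. Other block schemes.** These were simulated with equally likely sizes, an assumed 144 patients per stratum and 1000 runs. The observer sees everything and knows which sizes are possible.

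| Sizes | Certain | Guessed correctly |
|---|---|---|
| 4 only | 33% | 71% |
| 2 and 4 | 11% | 72% |
| 4 and 6 | 5% | 69% |
| 4, 6 and 8 | 2% | 68% |

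The row for 2 and 4 tests a kinder reading of the sentence, in which sizes vary up to 4. Certainty falls by two thirds, but the guess rate does not fall.

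**The case against.** The strongest reply is that the article condenses a full protocol (version 1.6) that is not shown, and the sentence may be loose wording for randomly permuted blocks of 4 or for sizes varying up to 4. That stands: a fixed size of 4 is an inference from contradictory words, not a stated fact. It does not remove the point, because step 3 shows that sizes 2 and 4 still leave predictable positions.

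Second, 33% and 71% describe a fully informed observer, and the article nowhere says that staff see every past assignment. This also stands. Because hospital is not a stratification factor, a shared list would hide part of the sequence from each site. For the same reason, having only two strata does not make matters worse: the 33% does not depend on the number of strata, and adding hospital as a factor would give each site a fully visible list.

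Third, a reader might infer that the nurse's spreadsheet is the source of the problem or has been misused. The article does not support that. The file is password-locked, the nurse is not said to recruit, and the investigators are the ones described as explaining the study to potential participants. Predictability comes from the small blocks and the open assignments. A password protects the file but does not stop inference from the past.

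Fourth, small permuted blocks in open-label trials are a common trade-off, and the article appeared about 5 months before the expected end of a recruitment period of about 32 months. Late timing limits how many patients a new list can protect. It does not excuse the contradiction or the unqualified concealment statement.

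**Conclusion.** The point holds as a self-contradictory description and an avoidable weakness in concealment. With blocks of 4, the share of assignments that can be known for certain ranges from about 8% (one-site observer seeing half of a shared list) to 33% (full sight of the stratum). The correct-guess rate ranges from about 60% to 71%. The lower ends rest on the assumed 50% share, and the upper ends on an observer who misses nothing.

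A reader might go further and conclude that the PSA or toxicity results are biased. The article does not support that, since nothing in it shows that anyone predicted an assignment or acted on a prediction. Physician-graded toxicity is in any case exposed to unmasked assessment, which no block scheme would change. The matter deserves correction because the risk is cheap to reduce; it does not by itself invalidate the trial.

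**What to change.** State the actual scheme: which block size or sizes are used, whether the hospitals share one list, and who releases assignments.

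For any patients still to be randomised, generate a new list per stratum with randomly varied block sizes, for example 4, 6 and 8. Do not disclose the sizes to sites, and have someone not involved in enrolment release one assignment at a time. This removes most of the certainty (33% to about 2% for a fully informed observer) but little of the guessing advantage (71% to about 68%), so non-disclosure and one-at-a-time release matter as much as the sizes.

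The cost is a new computer-generated list per stratum and a short amendment, with no extra staff. The downside is a final imbalance of up to 8/2 = 4 patients per stratum, against 4/2 = 2 with blocks of 4. Letting the open block finish before switching avoids adding to it.

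If recruitment has closed, report the block scheme that was used and who could see past assignments, and qualify the concealment statement accordingly.

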**Fig. 1 Fig1:**
[figure not shown]
Flowchart of study treatments. ^a^Risk groups defined according to the National Comprehensive Cancer Network (NCCN) guidelines. PSA, prostate-specific antigen; HRT, hypofractionated radiotherapy; CRT, conventionally fractionated radiotherapy; IMRT, intensity-modulated radiotherapy; EQD2, equivalent dose in 2-Gy fractions

As summarized in Table 3, the equivalent dose in 2-Gy fractions (EQD2) for the HRT regimen is 74.29 Gy, assuming an *α*/*β* ratio of 1.5 Gy for prostate cancer [38]. The HRT arm delivers a higher biologically effective dose (BED) than the CRT arm (173.33 Gy vs. 154 Gy). Assuming an *α*/*β* ratio of 10 Gy for acute-responding normal tissue, the BED is 81.25 Gy for the HRT arm versus 67.71 Gy for the CRT arm. Using an *α*/*β* ratio of 3 Gy for late-responding normal tissue, the HRT arm resulted in a BED of 119.17 Gy, which is slightly higher than the 110 Gy for the CRT arm.

**Table 3 Tab3:** Equivalent dose in 2-Gy fractions (EQD2) and biologically effective dose (BED) calculations

	Conventionally fractionated (66 Gy in 33 fractions)	Hypofractionated (65 Gy in 26 fractions)
EQD2^a^ (Gy)		
Prostate cancer	66	74.29
Early-responding normal tissue	66	67.71
Late-responding normal tissue	66	71.5
BED^a^ (Gy)		
Prostate cancer	154	173.33
Early-responding normal tissue	79.2	81.25
Late-responding normal tissue	110	119.17

^a^*α*/*β* ratio for prostate cancer is 1.5, 10 for early-responding normal tissue, and 3 for late-responding normal tissue

### Inclusion criteria

Eligible patients are required to have a diagnosis of histologically confirmed prostate adenocarcinoma after radical prostatectomy and must fulfill the following criteria: aged ≥ 19 years, an Eastern Cooperative Oncology Group performance status 0–1, intermediate or high risk according to the NCCN guidelines [37], and total serum PSA level after prostatectomy > 0.2 and ≤ 1.0 ng/ml. Patients should also have adequate bone marrow (absolute neutrophil count ≥ 1500 cells/mm^3^; hemoglobin concentration ≥ 8.0 g/dl; platelet count ≥ 50,000 cells/mm^3^), liver (total bilirubin < 1.5 times the maximum normal value; alanine aminotransferase or aspartate aminotransferase < 2.5 times the maximum normal value), and renal (creatinine < 2.0 ng/dl) function, as assessed by tests performed within the 6-month period prior to enrollment.

### Exclusion criteria

Patients are not eligible for inclusion if they have gross nodules detected in the prostate bed; clinical, radiographic, or pathologic evidence of nodal disease; presence of distant metastasis; prior neoadjuvant chemotherapy, cryosurgery, or brachytherapy of the prostate; prior pelvic RT or chemotherapy for any other disease; and any invasive malignancy diagnosed within 5 years of entry or if they have a severe active comorbidity.

